## Abstract

**Background:**

Lateral ankle sprains (LASs) are common injuries among military service members. Approximately 40% of individuals with an LAS progress to develop chronic ankle instability (CAI), a condition that results in substantial mechanical and neurophysiological impairment and activity limitation. Since proprioceptive and balance training improve functional outcomes and prevent secondary injury following LAS, they are recommended in clinical practice. Uneven treadmills are an innovative modality that challenge the sensorimotor system while performing an ecologically valid task simulating environments frequently encountered by service members with LAS and CAI.

**Objective:**

The aim of this study is to evaluate whether the inclusion of uneven treadmill training in standard rehabilitation can improve clinical, functional, biomechanical, and patient-reported outcomes compared with the standard of care alone in service members with LAS and CAI. The prophylactic effects of treatment on secondary injury and identification of any contributing or mediating factors that influence outcomes following treatment will also be evaluated. We hypothesize that service members receiving uneven treadmill training will demonstrate greater improvements in clinical and instrumented measures of impairment, patient-reported function, and lower risk of injury recurrence than the control group immediately post and 18 months following treatment.

**Methods:**

A multisite, parallel randomized clinical trial will be performed among service members aged 18-49 years being treated for LAS and CAI in military treatment facilities in the United States. Participants randomly assigned and allocated to receive the experimental intervention will be provided up to 12 sessions of training on an uneven terrain treadmill over a 6-week treatment course to supplement standard rehabilitation care. Treatment intensity of the rehabilitation exercises and treadmill training will be progressed on the basis of patient-perceived intensity and treatment responses. Outcome measures will include patient-reported outcomes, functional assessments, performance measures, and biomechanical measures. Investigators collecting outcome measures will be blinded to treatment allocation. Reinjury rates and patient-reported outcomes of function will be tracked over 18 months following treatment.

**Results:**

The project was funded in September 2020. Patient recruitment began in November 2021, with 3 participants enrolled as of February 2022. Dissemination of the main study findings is anticipated in 2024.

**Conclusions:**

This study will assess the impact of an innovative uneven-terrain treadmill on treatment outcomes in the rehabilitation of service members with LAS and CAI. The results of this study will be used to inform rehabilitation practices and to potentially improve functional outcomes and secondary prevention in this patient population.

**Trial Registration:**

ClinicalTrials.gov NCT04999904; https://clinicaltrials.gov/ct2/show/NCT04999904?term=NCT04999904

**International Registered Report Identifier (IRRID):**

DERR1-10.2196/38442

## Introduction

Lateral ankle sprains (LAS) are one of the most common injuries in the United States [1]. The burden of these injuries is even higher in the military, where the incidence is substantially greater in enlisted service members (21.3 to 33.4 per 1000 person-years) than in their civilian counterparts (19.0 to 26.6 per 1000 person-years) [1,2]. LAS substantially degrade the ability of the military to meet operational objectives, with an average of 14 days of lost duty time per injury [3] and more than 92,000 medical visits for the care of these injuries incurred per year [4]. While the burden of LAS determined by historical medical encounters is high, the true burden is likely much higher. Perceptions of LAS as a benign and self-limiting condition preclude care-seeking by service members [5]. Moreover, injury recurrence is common during the first 12 months following injury [6,7] and beyond [8]. Approximately 40% of individuals with LAS are projected to progress to develop chronic ankle instability (CAI) [8,9]—a complex clinical entity characterized by mechanical and sensorimotor impairments that result in long-term disability and degraded health-related quality of life [10].

Peripheral and central sensorimotor impairments are common in LAS and CAI. These neurophysiological deficits are the result of deafferentation from connective tissue and muscle injury, peripheral nerve injury, spinal- and cortical-level inhibition, changes in the cortical motor map, and central sensory reorganization [11]. For example, individuals with CAI demonstrate increased reliance on visual afference during dynamic tasks [12], which is a compensatory strategy to counter diminished plantar sensation [12-14]. Altered walking mechanics are also common in individuals with CAI, specifically a wider base of support, increased shank external rotation, a more plantarflexed and supinated foot, and a more laterally displaced path of center of pressure (COP) progression compared with uninjured individuals [15]. These adaptations are due, in part, to deleterious neuromotor changes in function, which affect the response time to lateral perturbations and reduce the ability to counter ankle inversion to prevent reinjury [11,15].

Based on the burden and morbidity associated with LAS and CAI, proper management of these injuries is especially salient in service members. This population has high physical demands and esoteric occupational and environmental exposures that increase injury risk [2]. Clinical practice guidelines for the treatment of LAS recommend inclusion of early progressive weight bearing, manual therapy, and functional exercises that include proprioceptive balance training [16]. These updated guidelines further recommend these exercises for secondary prevention of subsequent injury and outline the necessity for graded exposure to occupational-related tasks [16]. Proprioceptive training has been shown to improve some of the postural control deficits and COP excursions in patients with LAS and CAI [11] and to decrease the risk of reinjury [7,16]. Provision of therapeutic exercises, including proprioceptive training, early in the rehabilitation course has been shown to be prophylactic during the first 12 months following LAS [7].

Despite the demonstrated benefits of proprioceptive training and early rehabilitation following LAS, there is no evidence to suggest that the burden of CAI is decreasing. Currently, most proprioceptive training encompasses the use of static balance exercises performed on solid and compliant surfaces [17]. While static exercises are indeed important as part of a comprehensive rehabilitation course, they have limited ecological validity and may not provide the specificity needed to prepare service members for environmental hazards frequently encountered in the performance of occupational duties. Treatment modalities that provide graded exposure to perturbations during functional activity may better help to facilitate sensorimotor plasticity and integration in preparation for return to duty [11]. The purpose of this pragmatic randomized controlled trial is to determine if incorporation of graded exposure on an uneven-terrain treadmill during standard rehabilitation care will lead to greater improvement in function and secondary preventive effects than standard rehabilitation care alone in military service members with LAS and CAI up to 18 months following treatment. The secondary aim of this is to identify the factors that predict and mediate treatment outcomes in this population.

## Methods

### Study Design

This study will use a multisite, parallel randomized clinical trial, with Group (control and experimental) and Time as the independent variables. Methodological development was informed using the PRagmatic Explanatory Continuum Indicator Summary (PRECIS-2) tool [18]. The CONSORT (Consolidated Standards of Reporting Trials) statement for randomized trials of nonpharmacologic treatments [19] and the Template for Intervention Description and Replication (TIDieR) checklists [20] were used to guide reporting in this protocol.

### Recruitment

A total of 312 participants (LAS: n=156; CAI: n=156) will be recruited across 3 sites in the Military Health System (MHS), including the Naval Medical Center San Diego, California, the Naval Hospital Camp Pendleton, and the San Antonio Military Medical Center from November 2021 to approximately March 2023. Individuals who incurred a recent LAS and were assessed in the MHS will be identified using the electronic medical records and be contacted to discuss their interest in participation. Patients referred by primary care and specialty care clinics will be provided information on the study and an opportunity to participate. All treatments will be delivered in an outpatient physical therapy clinical setting.

### Inclusion and Exclusion Criteria

Individuals aged 18-49 years will be recruited to participate. Inclusion in the LAS stratum will require the occurrence of a substantial first-time sprain up to 2-6 weeks prior to obtaining consent, which limits functional activity for at least 1 day. Participants must be able to walk community distances without an assistive device and with a score of ≤4 out of 10 reported on the numeric pain rating scale (NPRS). Inclusion in the CAI stratum requires a history of at least one significant sprain greater than 12 months prior to consent, continued perceived or episodic “giving way” of the ankle, and reported decreased function on the Foot and Ankle Ability Measure (FAAM) activities of daily living (ADL) subscale (score≤90), FAAM Sports subscale (score≤80), and Cumberland Ankle Instability Tool (CAIT; score<24) [21]. Individuals will be excluded if they have previously undergone ankle surgery, had joint realignment owing to fracture, had recent (within the last 3 months) injury to other lower-limb joints, have a diagnosed connective tissue disorder (eg, Marfan syndrome or Ehlers-Danlos syndrome), have a neuromuscular disease or balance impairment (eg, visual or vestibular disorder) that precludes standing or walking, are pregnant, have nonremovable casting, or are unable to walk at enrollment.

### Ethical Considerations

The study protocol was approved by the institutional review boards at the Naval Medical Center San Diego, the Naval Health Research Center, and the US Army Regional Health Command-Central in compliance with all applicable Federal regulations governing the protection of human subjects. Research data were derived from an institutional review board–approved Naval Medical Center San Diego protocol (NMCSD.2020.0028). All participants will be required to provide informed consent prior to study enrollment. Recruitment of military service members will occur in the absence of supervisory staff to avoid any perceived coercion. Participants will also be free to withdraw at any time during the study. Because this study is being conducted within the MHS, all participants who decline to participate in this research will still be provided standard rehabilitation care.

### Intervention

#### Overview

Once consented and enrolled, participants will be randomly assigned to either the experimental or control arm at each site using a concealed, random blocked sequence. Stratified randomization will be used to ensure an equal number of men and women are assigned to both the control and experimental groups in the LAS and CAI strata. Group allocation information will be concealed using a password-protected electronic form that will be opened by an uninvolved research staff member and communicated to the treating clinician. Both experimental and control groups will be provided standard rehabilitation care—treatment that is guided by the recent revision of the clinical practice guideline promulgated by the Academy of Orthopaedic Physical Therapy [16] on the basis of clinician experience and patient values.

Participants allocated to the experimental group will also be provided a complementary progressive treatment under the supervision of a licensed physical therapist, consisting of walking on a custom uneven-terrain treadmill (Woodway, Inc) (Figure 1) that simulates negotiation of rocky terrain (Multimedia Appendix 1) [22] for approximately 30 minutes, twice weekly, for a maximum of 12 treatments until discharge from rehabilitation. Treatment will be advanced through 3 phases of activities based on observed performance and the participant’s perceived difficulty and symptom response. Each phase will contain activities that are broadly grouped by the intensity of the proprioceptive stimulus and will be completed on the uneven treadmill. All treating physical therapists will adhere to a single training protocol to ensure standardized delivery of the uneven treadmill training across all the participating sites.

**Figure 1 figure1:**
[figure not shown]
The custom uneven-terrain treadmill. Participants allocated to the experimental treatment will be provided a progressive gait retraining program in addition to standard rehabilitation care.

#### Experimental Treatment Progression

##### Phase 0: Familiarization

Participants will begin a familiarization trial during which they will walk on the treadmill at a low velocity (≤1.34 m/s) set at a level grade for at least 5 minutes while wearing an ankle brace. Continued use of the handrails for balance and offloading the injured limb will be allowed during this phase. Criteria for progression will depend on the symptom response, patient confidence, and the observed ability to walk unassisted.

##### Phase 1: Unloaded Treadmill Walking

Walking velocity will be progressively increased, and the ankle brace will be weaned on the basis of the pain response and perceived instability. As the participant acclimates to the activity, task difficulty will be incrementally progressed by manipulating the walking velocity, grade, and duration in accordance with patients’ perceived difficulty and performance observed by the treating clinician.

##### Phase 2: Unloaded Treadmill Walking With Head Movement and Visual Manipulation

Building on phase 1, the purpose of this phase is to encompass the integration of head movement, visual occlusion, and distraction. The following conditions will be integrated to increase task difficulty, as appropriate:

Low light condition: dark sunglasses (Sunglass Couture, Inc) will be used to reduce the amount of ambient light.Foot obscurement: foot placement will be obscured with dribble glasses (Liberty Imports) that obstruct participants’ view of the ground while carrying an inert training rifle (Ring’s Manufacturing Inc).Head turning: during the head turning activity, participants will be instructed to walk while turning their head right, left, upward, and downward.Distracted walking: during the distracted walking activity, participants will walk while playing a handheld electronic game (Classic 5 In 1 Poker, John N. Hansen Co, Inc).

##### Phase 3: Return to Duty and Recreational Running Tasks

The criteria for progression to this phase are met when the participant begins the transition from walking to running activities and has a FAAM ADL subscale score of >90 and FAAM Sports subscale score of >80.

Load carriage: the integration of a 12-kg load carried in a backpack (SOG Specialty Knives & Tools) will be included in phase-1 and -2 activities.Uneven trail running: integration of jogging (<2.78 m/s) and running (≥2.78 m/s) may be optionally performed in preparation for return to duty or recreational running.

### Outcome Measures

A series of clinical, instrumented, and patient-reported outcome measures will be collected to characterize ankle-foot impairment, activity limitation, and participation restriction at baseline, during treatment, and longitudinally following treatment. Figure 2 shows the CONSORT flow diagram that details the study time points. The primary outcome of interest is improvement in patient-reported function on the FAAM. To help elucidate clinical improvement in function, we will assess if the intervention has shifted COP progression more medially during walking and if recurrence of subsequent ankle injuries has been reduced. Reinjury count data will be collected and assessed in both groups.

**Figure 2 figure2:**
[figure not shown]
The CONSORT (Consolidated Standards of Reporting Trials) flow diagram. ADL: activities of daily living subscale, CAIT: Cumberland Ankle Instability Tool, EMG: electromyography, FAAM: Foot and Ankle Ability Measure, Godin: Godin-Shepard Leisure-Time Physical Activity Questionnaire, LEFS: Lower Extremity Functional Scale, NPRS: numeric pain rating scale, SEBT: Star Excursion Balance Test, TSK: Tampa Scale of Kinesiophobia.

### Patient-Reported Outcomes

The CAIT [23] is a 9-question instrument examining ankle pain and feelings of instability. The FAAM ADL and Sports subscales [24,25] and the Lower Extremity Functional Scale [26] assess difficulties in performing a variety of tasks. The NPRS [27] and Tampa Scale of Kinesiophobia [28] will be used to assess the participants’ pain and fear of movement due to the injury. Physical activity will be classified using the Godin-Shepard Leisure-Time Physical Activity Questionnaire [29] modified to record activity over the previous week rather than a typical week. These patient-reported outcomes will be recorded at all data collections (baseline, 2 interim sessions, discharge, and 6 postintervention follow-up assessments). Unstructured feedback requesting perceptions on participation in the uneven treadmill rehabilitation protocol will also be collected.

### Clinical Measures

Clinical measures of ankle dorsiflexion (unloaded and loaded), plantarflexion, inversion, and eversion; forefoot on rearfoot inversion and eversion; and strength measures of dorsiflexion, plantarflexion, inversion, eversion, and hallux and lesser toe flexion will be performed, as described by Fraser et al [30]. The Star Excursion Balance Test evaluates dynamic balance and control by asking the patient to reach as far as possible along a measuring tape affixed to the floor in anterior, posteromedial, and posterolateral directions while maintaining balance on the supporting foot [31,32]. Failure to maintain balance, hands on the hips, or weight shift onto the reach limb will constitute a mistrial and will be repeated. Agility, speed, and power will be assessed using the side hop test [33], Edgren Side Step Test [34], and the T-test [34]. The side hop test records how many times a patient can hop back and forth on one limb over a distance of 30 cm in 30 seconds [33]. The Edgren Side Step Test has participants side-step back and forth over a 4-m course for 10 seconds [34]. The T-test measures the time to run 40 m multidirectionally over a T-shaped course [34]. Participants will be provided familiarization of the tests and practice trials prior to collection. Verbal encouragement will be provided during assessments.

### Biomechanical Measures of Walking

Electromyography (EMG) and plantar pressures will be collected while walking on a standard treadmill at a self-selected velocity. Plantar pressure data will be recorded at 50 Hz using a Pedar-X shoe insole (Novel Electronics, Inc). EMG data (Trigno Avanti, Delsys Inc, and Noraxon DTS) will be recorded at 1500 Hz or greater bilaterally using Ag/AgCl electrodes affixed to 6 muscles (tibialis anterior, fibularis longus, lateral gastrocnemius, rectus femoris, biceps femoris, and the gluteus medius). Electrode placement will be performed as described by Weiss et al [35]. Visual inspection of the waveform during resisted contraction of each muscle will ensure cross talk is minimized. EMG data collected during walking will be processed by (1) using a fourth-order Butterworth filter for band-pass filtering between 20 Hz and 400 Hz, (2) rectifying the data, and (3) smoothing using a fourth-order Butterworth low-pass filter at 10 Hz and normalized to quiet standing. To compare walking EMG data between sessions, the amplitude will be normalized to the mean root mean square of processed EMG data collected during quiet standing for each muscle [36,37]. Gait cycles will be identified using a force-sensitive resistor located under the heel to detect heel strike. Data from at least 15 consecutive strides will be collected during steady-state walking.

### Longitudinal Tracking of Reinjury

Injury count data derived following completion of the intervention will be employed to assess secondary preventive effects of the control and experimental treatments in the LAS and CAI strata. These follow-up data will be collected for 18 months. Both in-network and out-of-network medical care provided to service members will be captured by the MHS. Each recruiting site will conduct a chart review of the electronic medical record at the 6 posttreatment time points to assess for any additional medical care provided for ankle injuries in order to include physical therapy or surgical care. Participants will also be contacted directly to establish any secondary injury outcomes that were self-managed.

### Blinding

Any research staff collecting data at any time point will be blinded to group assignment. Owing to the nature of the intervention, blinding of the participants or the clinicians providing the uneven-terrain treadmill rehabilitation intervention will not be feasible. Data analysis will be performed by researchers and statisticians blinded to group assignments.

### Statistical Analysis

To assess whether the addition of the rocky treadmill intervention to standard-of-care physical therapy improves rehabilitation, 4 repeated measurements of several outcomes (eg, CAIT and FAAM) will be measured over the active intervention period of the study. The data will be analyzed using an analysis of covariance–type linear mixed-effects model with Group, Time, and Group×Time variables as fixed effects and subject-specific variables {intercepts, slopes} as random effects. The null hypotheses for both LAS and CAI populations are that the slopes of the control groups equal those of the treatment groups.

To identify predictors and mediators of successful or unsuccessful rehabilitation outcomes, a 2-level (hierarchical) Bayesian model will be used to connect participant-specific responses to 6 explanatory variables: {X1, . . . , X6} = {age, sex, body mass index, pain intensity, weight-bearing status, and initial injury severity} to the subject-specific variables {intercepts, slopes}. A directed acyclic graph detailing the results of the Bayesian linear model will be developed (Figure 3). The regression parameters from the hierarchical Bayesian model will be estimated using Bayesian inference with Gibbs Sampling software, which creates a Markov chain Monte Carlo simulation of all regression parameters.

To analyze the effect of the treatment on long-term reinjury rates between the 2 arms of the study, we will fit both logistic regression–type generalized linear mixed-effects (GLME) models to the data as well as Cox regression time-to-event models. The data that will be used in the analysis will be those obtained at baseline and during the postintervention period. In the GLME analysis, the response data will be (1) the self-reported survey instrument measure from the Patient-Reported Outcomes Measurement Information System and (2) the binary reinjury report (1/0). The GLME model will have Group, Time, and Group×Time as fixed effects and will use subject-specific variables {intercepts, slopes} as random effects. The null hypothesis of the GLME model is that the regression parameters associated with the Group and Group×Time effects are zero. In the Cox regression analysis, the response will be the time of suspension or the event along with a binary indicator of reinjury status, and the covariate will be Group. The null hypothesis of the Cox regression analysis is that the regression parameter associated with Group is equal to zero. In all analyses, a Bonferroni-type correction to the hypothesis test’s *P* values or α levels will be used to account for multiple testing.

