**Figure 3 figure3:**
[figure not shown]
The direct acyclic graph of the Bayesian model acts like a causal diagram. In the model, the explanatory variables {X1, . . . , X6}: age, sex, BMI, pain intensity, weight-bearing status, and initial injury severity. These variables causally affect the subject-specific slopes and the y-intercepts. However, the slopes and y-intercepts of the responses are not directly observed, so they are considered latent variables. In the diagram, the shaded circles are directly observed variables, and the unshaded circles are latent variables. The Bayesian model has 2 levels of hierarchy: the first one establishes the best fit line that goes through the observed subject responses; the second one establishes how the explanatory variables {X1, . . . , X6} affect the slopes and y-intercepts. The regression parameters {η_0_, . . . , η_6_} are those that affect the slope of the subject responses and, as such, are particularly important because they affect the healing rate. Variables that significantly affect the healing rate will be retained in the model if the credible intervals for the regression parameters {η_0_, . . ., η_6_} do not include 0.

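### The model assigned to the predictor-and-mediator aim contains no treatment term and no mediator path, so it can describe prognosis but cannot identify mediators

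*Protocol article*

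**What the plan says.** The aim appears in three places in the protocol article. The Introduction says "The secondary aim of this is to identify the factors that predict and mediate treatment outcomes in this population". The Objective in the abstract says that "identification of any contributing or mediating factors that influence outcomes following treatment will also be evaluated". The Statistical Analysis section states the purpose, "To identify predictors and mediators of successful or unsuccessful rehabilitation outcomes", and names a two-level hierarchical Bayesian model as the method.

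The covariates of that model are "age, sex, body mass index, pain intensity, weight-bearing status, and initial injury severity". The Figure 3 legend completes the specification. The first level fits a line to each participant's responses. The second level describes how the six covariates act on the slopes and intercepts, and the legend presents this action as causal. The parameters for the slope, which the legend treats as the healing rate, run from η0 to η6. The legend adds a retention rule: "Variables that significantly affect the healing rate will be retained in the model if the credible intervals for the regression parameters" exclude zero.

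The linear mixed model, the generalized linear mixed-effects model and the Cox model in the same section all name Group explicitly. This model does not.

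**The concern.** A mediator of treatment lies on the path from treatment to outcome. To identify one, an analysis needs the effect of treatment on the candidate and the effect of the candidate on the outcome given treatment. A model without treatment contains neither. If the plan is followed as written, covariates associated with recovery rate could be reported as mediators, or as causes of healing, when the analysis has shown only that they are prognostic. The article also gives this aim no other model that could supply the missing part.

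**Working it through.** The document gives no sample size, error rate or power for this model, so there is no stated figure to reproduce. The check is of structure.

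**1. Parameter count.** From the Figure 3 legend, η0 to η6 is 7 parameters. From the Statistical Analysis section there are 6 covariates. 7 = 1 intercept + 6 covariates, which leaves none for Group or Group×covariate.

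**2. What the pooled coefficient estimates.** Suppose the slope truly follows

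slope = α + βG + ΣγⱼXⱼ + ΣδⱼGXⱼ + error,

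with G = 0 for control and 1 for experimental. Allocation is equal (78 per group in Power and Sample Size) and, if the covariates are pre-randomisation values, G is independent of X in expectation. Leaving G out then gives

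ηⱼ = γⱼ + δⱼ/2,

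the average of the two arm-specific associations. Two illustrations with assumed values:
- γ = −0.3 and δ = 0.6, so the association is −0.3 in control and +0.3 in experimental: η = −0.3 + 0.6/2 = 0. Real effect modification disappears.
- γ = 0 and δ = 0.6: η = 0 + 0.6/2 = 0.3. This is the same value as a covariate with association 0.3 in both arms (γ = 0.3, δ = 0). Effect modification looks like prognosis.

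With no modification (δ = 0), η = γ. Omitting Group does not bias the prognostic association, so that part of the analysis is sound.

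**3. Mediation.** Let M = aG + u and slope = bM + c′G + error. The indirect effect is a×b. Estimating a needs G, and estimating b given treatment needs G and M together. The described model has no G, and its six covariates enter only as causes of slope and intercept, with no arrow from treatment to any of them. So a×b is not estimable from it.

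**4. Illustrative simulation.** There were 2,000 runs with 156 participants (78 × 2, one stratum), using least squares on participant slopes in place of the second level. All effects were assumed: treatment to mediator 0.8 SD, mediator to slope 0.5, Group×covariate 0.6 (the cancelling case above), residual SD 1. Mediation alone, modification alone, and both together were simulated. The model as written flagged its six coefficients at 4.8% to 5.5% on average, at a 5% test level. With the missing terms added, mediation was detected in at least 99.8% of runs in which it was present, and the interaction in 89% to 94%. No prognostic signal was built in, so the chance-level result follows from the set-up. The simulation illustrates steps 2 and 3; it does not forecast power for this trial.

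**5. Whether suitable measures exist.** The Patient-Reported Outcomes section records pain and kinesiophobia at baseline, two interim sessions, discharge and six follow-ups. The Outcome Measures section asks whether the intervention moves centre-of-pressure progression medially, which is itself a mechanistic question. Kinesiophobia and centre of pressure are not among the six covariates. Pain is, but with no link from treatment.

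**The case against.** The best defence has three parts. First, this is a condensed article; Figure 3 and the full analysis plan are not shown, and mediation detail often sits there. Second, predicting outcomes can simply mean prognosis, and the model does that without bias from omitting Group. Third, the analysis is secondary.

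The second and third parts stand and limit the point. The first does not remove it: the article states the covariates, both levels, the slope parameters and the retention rule, so this is a stated model that does not fit its stated aim.

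A reader might infer more than the document supports:
- *That the whole secondary aim is unanswerable.* The predictor half, read as prognosis, is answered. The document nowhere states an aim of finding treatment-response predictors.
- *That all six covariates are baseline values and so cannot mediate.* The text does not call them baseline, and pain is measured repeatedly. The safe statement is that even an on-treatment value could not be tested as a mediator of treatment without Group in the model.
- *That the retention rule has no error control.* The legend gives no interval level, and the Statistical Analysis section promises a Bonferroni-type correction in all analyses. How that applies to credible intervals is unclear, but no false-inclusion rate can be derived from the text.
- *That weight-bearing status hardly varies.* For the sprain stratum, "Participants must be able to walk community distances without an assistive device", but this does not fix how fully the limb is loaded, and the familiarisation phase allows handrails for offloading.
- *That adjusting for pain and weight-bearing blocks part of the effect of injury severity.* This needs a causal assumption that the document does not make.

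**Conclusion.** The point holds for mediation. The only model assigned to the aim has 0 of 7 slope parameters involving treatment and no treatment-to-mediator path, so no mediation claim can rest on it. Nor can it distinguish effect modification from prognosis, which matters only if differential response is of interest. The legend's causal reading is not supported for what are pooled associations. The prognostic part of the analysis can stand.

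This rests on reading η0 to η6 as one intercept plus six covariates and on the legend describing the unseen figure completely. Fitting the model separately by arm would help with differential response, but it is not stated and would still not give mediation. The issue deserves correction before analysis because a named secondary aim is affected; the primary comparison is not.

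**What to change.** Choose one of two routes.

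**(a) Keep the mediator aim.** Add Group to the second level, and Group×covariate terms if differential response is of interest. Exempt Group from the credible-interval retention rule. Specify a separate mediation model with named post-randomisation mediators already collected, such as interim kinesiophobia or pain, or centre-of-pressure progression where its measurement time precedes the outcome. Adjust for the baseline value of the mediator and use a later FAAM score as the outcome, so that mediator precedes outcome. State that the mediator is not randomised and that the result assumes no unmeasured confounding between mediator and outcome. Report the η coefficients as prognostic.

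**(b) Narrow the aim.** Restate it as identifying prognostic factors for recovery, remove mediators from the aim and the Statistical Analysis section, and replace the causal wording in the Figure 3 legend with wording about association.

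Route (a) costs a modest additional model and its specification. Route (b) costs only rewording, but gives up the mediation question. Neither needs new data or changes the primary analysis.
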